## Abstract

**Background:**

Tourette Syndrome (TS) is a neurological condition presenting chronic motor and phonic tics, and important degree of comorbidity. Considered an uncommon illness, it first becomes apparent during childhood. Current standard treatment only achieves partial control of the condition, and provokes frequent, and sometimes severe, side effects.

**Methods and design:**

Main aim:

To show that, with respect to placebo treatment, the combination of 0.5 mEq/Kg magnesium and 2 mg/Kg vitamin B_6 _reduces motor and phonic tics and incapacity in cases of exacerbated TS among children aged 7–14 years, as measured on the Yale Global Tic Severity Scale (YGTSS).

Secondary aims:

Assess the safety of the treatment.

Describe metabolic changes revealed by PET.

Measure the impact of the experimental treatment on family life.

**Methodology:**

Randomized, blinded clinical trials. Phase IV study (new proposal for treatment with magnesium and vitamin B_6_). Scope: children in the geographic area of the study group. Recruitment of subjects: to include patients diagnosed with TS, in accordance with DSM-IV criteria (307.23), during a period of exacerbation, and provided none of the exclusion criteria are met. Instrumentation: clinical data and the YGTSS score will be obtained at the outset of a period of exacerbation (t0). The examinations will be made after 15 (t1), 30 (t2), 60 (t3) and 90 days (t4). PET will be performed at the t0 and t4. We evaluated decrease in the overall score (t0, t1, t2, t3, t4), PET variations, and impact made by the treatment on the patient's life (Psychological General Well-Being Index).

**Discussion:**

Few clinical trials have been carried out on children with TS, but they are necessary, as current treatment possibilities are insufficient and often provoke side effects. The difficulty of dealing with an uncommon illness makes designing such a study all the more complicated. The present study seeks to overcome possible methodological problems by implementing a prior, phase II study, in order to calculate the relevant statistical parameters and to determine the safety of the proposed treatment. Providing a collateral treatment with magnesium and vitamin B_6 _could improve control of the illness and help reduce side effects.

This protocol was approved by the Andalusian Government Committee for Clinical Trials (Spain).

This study was funded by the Health Department of the Andalusian Regional Government and by the Healthcare Research Fund of the Carlos III Healthcare Institute (Spanish Ministry of Health).

**Trial Registration:**

Current Controlled Trials ISRCTN41082378

## Background

Tourette Syndrome (TS) is a condition that was first described in 1885 by Gilles de la Tourette as a clinical situation with significant tics, coprolalia and inappropriate behaviour. For several decades, it was considered a psychiatric disorder. This situation changed in the 1960s with advances in our understanding of neuroleptic drugs that made it possible to achieve some improvement in the symptoms presented by TS, now viewed as a neurological disorder. This observation constituted the beginning of the search for neurobiological factors for TS [1].

TS is currently considered a neurological condition with a genetic background and varying degrees of penetration, presenting chronic motor and phonic tics, sometimes accompanied by a comorbid pathology, and with a natural rhythm of remissions and exacerbations [2,3].

Diagnosis of TS is a clinical decision; it is defined as the presence of motor and phonic tics with an evolution exceeding one year, appearing during infancy or childhood (always before the age of 18 years) and often accompanied by a comorbid neurological disorder. This accompanying pathology is not always present, but normally determines the severity of the complaint. It consists of the existence of an attention deficit/hyperactivity disorder (ADHD), an obsessive/compulsive disorder (OCD) or other behavioural disorders such as poor control of impulses or a tendency to self-harm [2].

Tics are believed to be the most frequently occurring neurological disorder during childhood (up to 4%). Some authors have calculated the prevalence of TS to be 4–5 cases per 10,000 persons, counting all ages, but it is more frequent among children, affecting almost 1% of the juvenile population [4-7]. It predominantly affects males (75%). There is a clear tendency for various members of the same family to be affected, with varying degrees of severity, and it has been related with many chromosome sites, including 11q23. Symptoms among children are more intense when the transmission is bilinear (maternal and paternal) [2,8,9].

Tics can be motor and/or phonic, and may not initially be recognized as such. They begin as simple motor tics, frequently expressed by blinking or sniffing, while complex motor tics take the form of coordinated movements of the neck or unusual facial expressions. The presence of phonic tics is a diagnostic criterion; sometimes, these are simple, such as the emission of guttural sounds, while less frequently they take complex forms like echolalia or coprolalia, which are the most striking manifestations of the disorder. Although rare, the latter can have very negative consequences for the social and emotional life of the child.

Tics first appear at around the age of seven, beginning as simple ones and subsequently becoming more complex. By definition, they are long-lasting (more than one year's duration). They tend to worsen and improve over periods of two to three months. New tics may appear and others disappear, or reappear later. In general, tics evolve from simple to more complex forms, and from the head to the lower limbs. Great distress is caused to the child, who tries to suppress them, and may succeed for a limited time, after which they may suddenly reappear, stronger than ever. When tics are severe, they interfere with the life of the child [1,10].

The natural evolution of TS generally begins with ADHD at an early age (three or four years), with the first tics as such appearing at seven or eight years, first in the form of simple motor tics affecting the face, and then complex, intense and verbal. Subsequently, OCD may appear. The condition worsens at the age of ten to fourteen years, and usually improves by sixteen to twenty years. Fifty per cent of such patients are free of tics by the age of eighteen years, while the remainder continue to present the symptoms during adult life, although generally in a less intense, more manageable form that enables them to adjust and enjoy a normal social, family and emotional life [2]. Typically, the condition worsens in situations of stress or when catecolaminergic or corticoid medication is taken.

The pathogenesis of the complaint is not well understood, although family incidence is evident. The natural evolution during puberty, together with the greater incidence of tics among boys, are suggestive of a hormonal influence. One factor suggested is that of a synaptic neurotransmitter disorder resulting from the disinhibition of the cortical striatal thalamic circuit, on the basis of the relative degree of control achieved with neuroleptic medication [11-13]. Other possibilities suggested by the comorbid symptomatology (ADHD and OCD) are the basal ganglia (caudate nucleus) and the lower prefrontal cortex. However, postmortem examinations have failed to reveal specific alterations. No models of TS have been observed among animals. Neuroimaging studies are usually normal, although the presence of tics has been related to the presence of asymmetry in the basal ganglia [14]. It has been suggested that a disorder of the central neurotransmitters may give rise to TS, as a response to the modulation of the dopaminergic system; also mentioned as possible causes have been low levels of serotonin, glutamate and AMP; on occasion, too, PET has revealed an increased density of transported presynaptic dopamine and of D2 postsynaptic dopamine receptors [15-17]. Autoimmune phenomena have also been observed in this respect, with the presence of antineuronal antibodies against beta-haemolytic streptococci, as the case in other neurologic disorders (such as Sydenham chorea). It is in this context that the PANDAS syndrome (*Paediatric autoimmune neuropsychiatric disorders associated with streptococcal infections*) has been reported, although in the latter case, the appearance of tics is much more brusque [18]. The results of complementary studies of TS children are usually normal.

Treatment of TS is symptomatic. The tics are treated with neuroleptic blockers of dopamine receptors (D2), such as haloperidol. In recent years, other atypical neuroleptic drugs (pimozide, risperidone) have been incorporated into the treatment; these present fewer side effects, although they are not totally free of adverse reactions [19]. Some side effects, such as tardive dyskinesia may be severe and difficult to treat [20]. Clonidine (often with methylphenidate) is commonly used to treat Tourette's syndrome [1,2]. These drugs have been applied both singly and in combination, and in short term treatments (coinciding with periods of exacerbation) and long term ones [21-23].

ADHD is treated with amphetamines (methylphenidate) [24]. OCD is alleviated with the administration of antidepressives to inhibit serotonin reuptake (fluoxetine) [25,26].

In addition to pharmacological treatment, it is very important to provide suitable educational counselling for the child and his/her family. Cognitive-behavioural therapy can achieve an improvement in the comorbid pathology, especially as regards the obsessive-compulsive disorder [10].

### Background to the study

Other than in scientific texts, there exist anecdotal communications of the experiences of parents of TS children, reporting a significant decrease in the number and severity of tics suffered when certain multivitamin and mineral compounds were taken. This improvement, apparently, was notable but not total, and the symptoms generally reappeared when these substances ceased to be administered. This kind of communication constitutes a new physiopathological viewpoint, according to which a magnesium insufficiency might be the principal causative factor and the common pathway leading to the symptoms of TS and its comorbid pathology [27].

We wish to study whether any benefit is gained from the oral administration of magnesium and vitamin B_6 _to TS children. Both substances are commonly included in vitamin supplements for children and adults, they are considered very safe and may be acquired without a medical prescription.

Magnesium pidolate is taken as a syrup, at home. It is contraindicated for persons with illnesses such as decompensated or acute renal insufficiency, myasthenia gravis, diabetes or Cushing's disease. It should be utilized with care for patients with irregular calcium metabolism. The excipient may provoke allergic reactions, including asthma, especially among persons allergic to acetylsalicylic acid. No side effects have been described for therapeutic dosages. It should not be administered in conjunction with calcium (dairy products), which is prejudicial to its absorption.

Pyridoxine alpha-ketoglutarate could also be taken as a syrup, at home. No contraindications or side effects have been described, for therapeutic or even greater dosages. Its excipient, too, may give rise to allergic reactions, including anaphylaxia and bronchial spasms, especially among patients with a previous history of allergy or of asthma. It should not be mixed with other medicines, in order to preserve its absorption capacity.

We have designed a clinical trials to evaluate the effects of magnesium and vitamin B_6 _supplements on the clinical condition of children with TS. This supplementation is authorized for children and already commercially available; therefore, our aim in the present study is to confirm a possible new indication. The study should include children up to the age of 14 years, diagnosed with TS; this age limit was chosen as it is then when a standstill or remission of the symptoms may occur. The minimum duration of treatment and follow-up for these children should be three months, in view of the natural evolution of the illness, with spontaneous remissions and exacerbations. The symptoms most easily measured are the presence and severity of tics.

We present a new therapeutic approach to TS, based on the hypothesis that a deficit of vitamins or oligoelements, or a reduction of their activity, aggravates this pathology and often provokes severe comorbidity. Moreover, we take into account that current treatment protocols are frequently ineffective among many children and present important potential side effects.

Thus, we propose the following:

Main goal – to show that, with respect to placebo treatment, the combination of 0.5 mEq/Kg magnesium and 2 mg/Kg vitamin B_6 _reduces motor and phonic tics and incapacity in cases of exacerbated TS among children aged 7–14 years.

Secondary goals – to assess the safety of the treatment, in terms of adverse events; to describe metabolic changes resulting from the treatment, as revealed by PET; and to measure the impact of this treatment on the quality of family life.

## Methods and design

### Design

#### Type of clinical trials

Blind, randomized clinical study, Phase IV (new indication for supplementary magnesium and vitamin B_6_).

This study began in October 2007 and is currently in progress.

#### Recruitment of patients

The patients to be included are those diagnosed with TS, according to DSM-IV (307.23) criteria [28], currently in a phase of exacerbation. The primary healthcare paediatricians in the whole region were informed about the EECC, so that patients could be referred to the clinics where the study was being carried out. The doctors responsible for making the scale evaluation when a patient was included in the study referred him/her to the pharmacy department to be included in one of the two study groups, using the randomization table. Informed consent must be obtained from parents or guardians, and none of the exclusion criteria must be present. (See Figure 1).

**Figure 1 F1:**
[figure not shown]
**Patients flowchart**.

### Study subjects

#### Patients

Patients diagnosed with TS, aged 7–14 years, either sex, with a minimum score of 40 points on the *Yale Global Tic Severity Scale (YGTSS) *[29], among whom the onset of clinical exacerbation has been observed.

### Selection criteria

#### Criteria for inclusion

- Aged 7 – 14 years, either sex. This is the age bracket during which the natural course of the illness is most exacerbated. Before the age of 7 years, the tics may not yet have appeared (this generally occurs at the age of 5 – 7 years). After 14 years, symptoms tend to stabilise.

- Informed consent of the child's parents or guardians, and reasoned agreement with the child.

- Clinical diagnosis of TS, according to Diagnostic and Statistical Manual of Mental Disorders – Fourth Edition (DSM-IV) criteria.

- Score of 40 or more on the YGTSS.

#### Criteria for exclusion

- Severe ADHD or OCD, not clinically controlled.

- Severe TDAH or TOC, not clinically controlled.

- Autism.

- Unrelated depression.

- Allergy to acetylsalicylic acid (due to the excipients used).

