#### Randomization criteria

- Criteria set out above (age, diagnosis, consent).

- Evidence of exacerbation (Score ≥40 on the YGTSS).

- No contraindication due to the exclusion criteria.

- Patients who fulfil these criteria will be included, randomly, in one of the groups.

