#### Randomization, blinding and assignment to treatment group

Randomization will be centralized and performed immediately after the inclusion of an eligible patient. The allocation envelopes will be serially numbered to ensure that allocation concealment is maintained within the pharmacy department at each hospital. A set of opaque envelopes marked with the letter A or B will be used to include patients in either the experimental or the control group. These envelopes will be kept in the pharmaceutical department responsible for dispensing the corresponding medication. Randomization to either the treatment or the placebo group will only be performed when a patient, suffering exacerbated TS, is considered eligible to receive the medication included in this study.

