#### Withdrawal of individual patients

Patients may withdraw from the study at any time, for any reason and without suffering any sanction for doing so. The researcher-collaborator, after consulting with the principal investigator and the study coordinator, may also interrupt the treatment programme if the fact of continuing this treatment, in his/her opinion, would be prejudicial to the patient's welfare. If a patient withdraws or is withdrawn from the study, follow-up to day 90 should be continued whenever possible.

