The composition of multivitamin and mineral compounds is very diverse, but from a theoretical standpoint, taking into account their pharmacological properties and following the hypothesis set out above, we consider that clinical trials should be focused firstly on the administration of magnesium and vitamin B_6_. Both substances present a wide therapeutic margin and have very few side effects; moreover, they are authorized for similar indications among children and have a long history of therapeutic use.

Magnesium ions are fundamentally intracellular or located in the bones, with only 1% being extracellular; in consequence, magnesium levels in plasma do not accurately reflect the content in the body. Traditionally, it has been used intravenously to treat severe nutritional deficit, as an antiarrhythmic agent and in cases of eclampsia-preeclampsia. Orally-administered magnesium has been used as a nutritional supplement. It can be given to children. It is contraindicated in cases of acute or chronic decompensated renal insufficiency, myasthenia gravis, diabetic coma and Cushing's disease. The recommended physiological dose is 0.2–0.5 mEq/kg/day [51].

Vitamin B_6 _(pyroxidine) is a hydrosoluble vitamin with a wide therapeutic margin. In clinical and pharmacological trials, it has been shown to have interesting properties, participating in oxidative deamination, transamination and decarboxylation; it also participates in the decarboxylation of glutamic acid to GABA, from DOPA to dopamine and from 5-hydroxytrytophan to seratonin. It presents anti-convulsant properties and seems to exercise a neuroprotective and antitoxic effect. It can be administered to children, and has been authorized for use to treat children with alterations in character, language and behaviour; learning difficulties; delayed learning to walk; convulsive illnesses; intoxication of the central nervous system; trembling; and Parkinson's disease. The dosage provided may vary widely, as renal elimination ensures its toxicity is minimal [52].

As the activity of magnesium is a consequence of its ion fraction, it is mainly intracellular and bears little correlation with the magnesium in serum. We do not believe clinical conclusions can be drawn from the measuring of magnesium levels in serum [53]. In the same way, determining the levels of vitamin B_6 _in serum would not be useful, in view of the fact that the problem lies in the activity deficit [48].

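### The exclusion list omits all four categories of magnesium contraindication that the protocol itself states

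*Protocol article*

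**What the plan says.** Two places in the protocol article state when magnesium must not be given. On magnesium pidolate, Background to the study says: "It is contraindicated for persons with illnesses such as decompensated or acute renal insufficiency, myasthenia gravis, diabetes or" Cushing's disease. The Discussion says that oral magnesium is "contraindicated in cases of acute or chronic decompensated renal insufficiency, myasthenia gravis, diabetic coma" and Cushing's disease.

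Criteria for exclusion has five bullets: severe uncontrolled ADHD or OCD; severe uncontrolled TDAH or TOC; autism; unrelated depression; and "Allergy to acetylsalicylic acid (due to the excipients used").

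Three sections govern entry:

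- Recruitment of patients: "Informed consent must be obtained from parents or guardians, and none of the exclusion criteria must be present".
- Randomization criteria: one condition is "No contraindication due to the exclusion criteria", and the section closes with "Patients who fulfil these criteria will be included, randomly, in one of the groups".
- Randomization, blinding and assignment to treatment group: randomization "will only be performed when a patient, suffering exacerbated TS, is considered eligible to receive the medication included in this study".

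**The concern.** The protocol says that children with certain illnesses should not receive the study drug, but the list that decides who enters does not mention those illnesses. The omission does not look deliberate. The acetylsalicylic acid exclusion comes from the same Background paragraph as the contraindications, so a warning about possible allergic reactions to the excipient became an exclusion while the outright contraindications did not. The article gives no reason for the difference.

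What is at stake is the safety of children aged 7 to 14 who take the medication at home and are first seen again at day 15. Nothing in the sample size or the primary analysis depends on this point.

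**Working it through.** No sample-size, power or error-rate figure is involved. The check sets the stated contraindications beside the entry rules.

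**Step 1. Contraindications against exclusions.**

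| Category | Background to the study | Discussion | Criteria for exclusion |
|---|---|---|---|
| Renal insufficiency | decompensated or acute | acute or chronic decompensated | absent |
| Myasthenia gravis | yes | yes | absent |
| Diabetes | diabetes | diabetic coma only | absent |
| Cushing's disease | yes | yes | absent |

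Covered: 0 of 4. Three categories are given consistently in both places; the fourth differs in breadth. The inclusion criteria (age, consent, diagnosis, YGTSS score) do not cover any of them either.

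**Step 2. What the list does contain.** There are five bullets. The first two appear to be the same exclusion, once with English and once with Spanish abbreviations, which leaves 5 − 1 = 4 distinct exclusions. One of these four, the acetylsalicylic acid allergy, relates to the drug; the other three are psychiatric or developmental.

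**Step 3. Is the printed list the working gate?** Recruitment of patients requires that no exclusion criterion be present. The Randomization criteria define the contraindication check by reference to the exclusion criteria and then say that patients who meet the conditions will be included. The only explicit contraindication check in the article thus points to a list that lacks the magnesium contraindications.

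**Step 4. Is other illness ruled out in some other way?** No. Other medication allowed lets children continue treatment prescribed for other concurrent illnesses, so such children are expected in the trial. The t0 procedures in Study periods are the YGTSS, the baseline PET and the parents' PGWBI; no check for these four conditions is listed.

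**Step 5. What safeguards remain?** The requirement that the patient be considered eligible to receive the medication applies before randomization, but names no condition. The pharmacy prepares and dispenses the medication, and those sections name no condition either. Under Withdrawal of individual patients, the researcher "may also interrupt the treatment programme if the fact of continuing this treatment, in his/her opinion, would be prejudicial" to the patient's welfare, but this applies only after enrolment.

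**Step 6. Dose.** The trial gives 0.5 mEq/kg/day (Dosage and administration of medication). The Discussion recommends 0.2–0.5 mEq/kg/day, so the dose is within the range and at its upper limit. A dose within the recommended range does not remove a contraindication stated alongside it.

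**The case against.** The strongest reply is that the requirement to be considered eligible to receive the medication is itself written, restrictive and in the Methods. A child for whom magnesium is contraindicated is not eligible to receive it, and the Background tells a clinician which illnesses matter. On this reading the gap is one of explicitness and opens no route to enrolment. Much of this stands: it is a real safeguard, and it lowers the risk. It does not close the gap, because the operative sections never say which diseases to look for.

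Second, this is a journal article, and the full protocol may hold a longer list; the duplicated bullet suggests loose editing. That would excuse an absent or summarised list. Here a specific list is printed, randomization is tied to it, and it does not match safety statements in the same article. Whether screening in practice was fuller cannot be told from this text.

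Third, the Background wording is illustrative, and diabetes and diabetic coma are different conditions, so the four categories are tidier than the source. That is fair for diabetes. The other three categories appear in both places.

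Fourth, acute renal insufficiency and diabetic coma are unlikely in a child attending a clinic for worsening tics, and treatment or the study can be stopped if harm appears. This supports a modest view of the risk. It does not justify leaving the listed criteria open to a child whom the protocol says should not receive the drug.

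**Conclusion.** The concern holds. None of the four stated contraindication categories appears in the exclusion list, and the protocol's explicit contraindication check relies on that list. A child with one of these conditions meets the listed criteria and is kept out only by a general judgement of eligibility.

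This should be fixed as a matter of patient safety and internal consistency. The practical risk is probably low, but that is a judgement: the article gives no frequency for these conditions among candidates, so no percentage is offered. The conclusion rests on the printed list being the working list, as Recruitment of patients and the Randomization criteria present it. The difference between diabetes and diabetic coma lies in background and discussion text; it makes nobody eligible by itself and is a secondary point.

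**What to change.** 1. Add to Criteria for exclusion now: acute or chronic decompensated renal insufficiency, myasthenia gravis, and Cushing's disease.
2. Add a check for these conditions to the t0 procedures in Study periods, before randomization. The existing contraindication check and the general eligibility requirement then cover them without further change.
3. Separately, have the responsible clinicians decide whether all diabetes or only diabetic coma is the contraindication, add that wording to the exclusion list, and align the Background and the Discussion. This need not delay steps 1 and 2.

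The cost is a short amendment and an updated t0 checklist. The trial has been running since October 2007, so the amendment concerns an approved trial in progress and would protect the children still to be enrolled. The downside is possibly a few lost candidates, mainly if all diabetes is excluded, in a trial whose Discussion already expects recruitment to be difficult.
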